### Participant withdrawal criteria

Participants who meet the criteria summarized in Table 3 will be discontinued from the trial. The subjects who are withdrawn after randomization will be followed up for outcomes. Reasons for withdrawal will be documented in case report forms (CRF) and data will be analyzed using the intention-to-treat (ITT) principle. Each site research coordinator will be responsible for making next-visit reminder phone calls to prevent a participant’s withdrawal.

**Table 3 Tab3:** Participant withdrawal criteria of the *Sipjeondaebo-tang* study

Participant withdrawal criterion	
1. Those whose medication compliance is < 70%	
2. Those who become pregnant during the study period	
3. Those who need surgery or inpatient treatment due to emergencies such as accidents or other illnesses	
4. Subject’s withdrawal of consent	
5. Subjects who have received prohibited medicines or therapies (e.g., anticoagulants, psychotropic drugs, and other drugs that may affect the symptoms of CHHF)	
6. Those who need standard treatment due to deterioration of symptoms of CHHF	
7. Occurrence of a serious adverse event	
8. Occurrence of factors making it difficult to sustain the process or investigator’s decision to terminate because of clinical trial results affected by some factors	

*CHHF* cold hypersensitivity in the hands and feet

### Randomization

Suitable participants, who agree to participate in this RCT, will be randomly assigned to a treatment group (SDT) or a placebo group at a 1:1 ratio. Thirty subjects will each be allocated to the SDT and placebo groups. A web-based randomization system (WBRS) developed by the contract research organization (CRO), the Institute of Safety and Effectiveness Evaluation for Korean Medicine (ISEE), will perform the assignment. The random order will be generated by the CRO’s independent professional statistician using the SAS 6.1 program and stratified by the hospital using random block sizes of two and four based on the allocation code provided by the SAS system.

### Blinding

Both the researchers and the subjects will be blinded to the assignment of study drugs. The sponsor’s CRO will label the randomization code number on the clinical trial drugs. The labeled trial products will be provided to clinical trial sites by the CRO. The same number of clinical trial medicines as the randomization number assigned via the WBRS will be administered to each subject by independent research pharmacists or assistants who are also blinded to the randomization, in each hospital. In the event of urgent medical conditions, such as serious adverse events (SAEs) or voluntary withdrawals, the principal investigator of the hospital will inform the CRO and sponsors immediately to process the unblinding in accordance with the ISEE’s standard operating procedures (SOPs).

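### The Blinding section names voluntary withdrawal as an occasion for unblinding, although withdrawn women stay in outcome follow-up and in the ITT analysis

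*Protocol article*

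**What the plan says.** The Blinding section promises that "Both the researchers and the subjects will be blinded to the assignment of study drugs". It then sets the rule for breaking the code. The condition is an urgent medical one, and the examples and the action follow in one sentence: "serious adverse events (SAEs) or voluntary withdrawals, the principal investigator of the hospital will inform the CRO and sponsors immediately to process the unblinding", under the CRO's standard operating procedures. Those procedures are not part of the article.

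The section on participant withdrawal criteria states: "The subjects who are withdrawn after randomization will be followed up for outcomes". It adds that reasons for withdrawal are recorded and that "data will be analyzed using the intention-to-treat (ITT) principle". Its Table 3 has eight reasons. Withdrawal of consent is item 4. Emergencies needing surgery or admission (item 3) and serious adverse events (item 7) are separate items.

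The primary outcome is the change in a 0 to 10 cm coldness VAS from visit 2 to visit 4. The study schedule (Table 4) places a blindness test at visit 4, and the AE reporting section requires a causality judgement for every adverse event. Randomization is "stratified by the hospital using random block sizes of two and four".

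**The concern.** The two sections do not fit together. One gives withdrawal as an example of an urgent medical condition that leads to a code break. The other treats withdrawal of consent as a reason distinct from medical emergencies, and asks that withdrawn women go on supplying outcome data. Nothing in the article limits a code break to cases where the woman's care depends on knowing her arm.

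The VAS is a subjective rating, so blinding is the main protection of the primary comparison. If a woman or the staff seeing her learn the allocation at withdrawal, her later ratings, the causality judgements and the blindness test can all be influenced by that knowledge. Women who stop may also differ from those who continue.

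**Working it through.** **1. The sections side by side**

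| Question | Blinding | Withdrawal criteria and Statistical analysis |
|---|---|---|
| Is voluntary withdrawal a medical emergency? | Given as an example of one | Withdrawal of consent listed apart from emergencies and SAEs |
| What happens to the code? | Unblinding is processed | Not mentioned |
| Are outcomes still collected? | Not mentioned | Yes |
| Are they analysed? | Not mentioned | Yes, by ITT; missing values filled by LOCF |
| Who receives the code? | Not stated; left to procedures not shown | Not stated |

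**2. When a break can reach the primary outcome.** If the code is opened before visit 4 and the woman still attends, her visit 4 VAS is given after the break. If she attends no further visit, LOCF carries forward an earlier VAS, normally taken before the break. If the break comes after visit 4, the primary outcome is untouched.

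**3. How many women.** The inputs are in the sample size section: difference 11.85, SD 15.255, dropout 13%, 30 per arm. Power is not stated; 80% is assumed, with two-sided alpha 0.05.

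- n per arm = 2 × [15.255 × (1.960 + 0.842) / 11.85]² = 26.02
- 26.02 / (1 − 0.13) = 29.9, so 30 per arm. The plan's figure is reproduced.
- 0.13 × 60 = 7.8 women. This is dropout for all reasons, so it is a ceiling.
- If half of the dropout were voluntary with continued follow-up (assumed): 0.5 × 7.8 = 3.9. If a quarter: 0.25 × 7.8 = 1.95. If none: 0.

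**4. What that could do to the estimate (illustration).** Suppose 13% of each arm were unblinded before visit 4 and still rated, and the between-group difference among them moved by the whole planned effect. The ITT difference would then move by 0.13 × 11.85 = 1.5 mm, or 1.5 / 15.255 = 0.10 SD. With half as many women it would move by 0.065 × 11.85 = 0.8 mm. The documents do not show how large the shift would be.

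**5. What one break tells about other women.** Assume that block sizes two and four are equally likely and that five equal sites recruit 60 / 5 = 12 women each.

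- First two women at a site in opposite arms: 0.5 × 1 + 0.5 × 2/3 = 0.83.
- Long-run average for neighbours, taking one block of each size (one pair inside the block of two, three pairs inside the block of four, two pairs across boundaries): (1 + 3 × 2/3 + 2 × 0.5) / 6 = 0.67.
- Enumerating every allocation sequence for a 12-woman site gives 0.54 to 0.83 for neighbours, depending on position.
- Best-guess success for the other women at that site, and share whose arm can be deduced with certainty:

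| Codes broken at the site | Mean correct guess | Certain deduction |
|---|---|---|
| 0 | 50% | 0% |
| 1 | 54% | 0% |
| 2 | 58% | 0.3% |
| 3 | 61% | 1.3% |

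After one break, the best guess for the single most exposed woman is right 78% of the time. The ceiling of 7.8 breaks is 7.8 / 5 = 1.6 per site.

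**The case against.** The strongest reply is that the sentence is governed by urgent medical conditions, with withdrawal only an example. It may therefore mean withdrawals that arise in a medical emergency. How the code is released is left to procedures that an article would not normally reproduce. A woman who withdraws consent, the only clearly voluntary reason in Table 3, may give no further data, and LOCF then uses a value from before the break. The trial is a pilot, and 50 of 60 women had been recruited at publication.

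Much of this stands, and it limits the size of the point. It does not remove it. The procedures are cited for how unblinding is processed, whereas the article itself names withdrawal as an occasion for it. If only medically urgent withdrawals are meant, the words add nothing and invite a wider reading at the sites.

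Three stronger readings are tempting, and the documents support none of them:

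- **Every withdrawal will be unblinded.** The wording is ambiguous and does not clearly order this.
- **Unblinded staff will collect the VAS and judge causality.** No section says whether the woman, the site staff, or only the CRO and sponsor receive the code. That the VAS is self-rated is likewise inferred from its anchors.
- **Small blocks expose the women still on treatment.** The 0.83 holds only for the first two women at a site. Mixing two block sizes hides the boundaries, so the average gain in guessing after one break is about 4 percentage points, and only if site staff learn the code.

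**Conclusion.** The point holds as an inconsistency between the Blinding and withdrawal sections that should be corrected. As written, the plan allows a code to be broken without medical need for a woman whose subjective outcome still counts in the ITT analysis. The effect is possible, not certain. It requires a woman who stops voluntarily, whose code reaches her or her site, and who still attends a later visit. The ceiling is about 8 of 60 women, the true number may be far lower, and the documents do not allow it to be estimated. Leakage to other women is secondary and rests on assumed equal block-size probabilities and equal sites. The sample size and the planned tests are unaffected.

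**What to change.** - Delete voluntary withdrawals from the unblinding triggers in the Blinding section, and state in the withdrawal section that withdrawal alone does not break the code.
- Keep the codes of withdrawn women closed to site staff and participants until database lock, unless an emergency requires the allocation to be known.
- Log every code break with its reason, who was told, and its date relative to visit 4. Report the number of breaks by arm, including any that have already occurred.

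The cost is one sentence and a memo to the five sites. The small downside is that women who withdraw learn their allocation only at study end. With 50 women already recruited at publication, the change protects only those still to be enrolled or still in follow-up. For the others, the log shows whether the issue arose.

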### Procedure

#### Recruitment

Participants will be recruited from five Korean medicine university hospitals located in various cities in Korea. Each institution will recruit the persons who have visited each clinical institute for clinical trials or through public outdoor advertisement.

#### Study schedule

The items to be measured at each visit are presented in Table 4.

**Table 4 Tab4:** Study schedule for the trial

	Screening	Treatment period			Follow-up
	Visit 1 (day − 7 to − 2)	Visit 2 (day 0)	Visit 3 (day 28 ± 3)	Visit 4 (day 56 ± 3)	Visit 5 (day 84 ± 3)
Informed consent	●				
Inclusion/exclusion criteria	●				
Randomization		●			
Drug compliance			●	●	
Vital signs	●	●	●	●	●
Body measurement^a^	●	●	●	●	●
Demographic, sociological, and gynecological information^b^	●				
Medical history^c^	●	●	●	●	●
General physical examination	●	●	●	●	●
Thermometer measurement^d^	●	●	●	●	●
Visual Analogue Scale	●	●	●	●	●
Adverse event monitoring			●	●	●
Pattern Identification Questionnaire	●				
WHOQOL-BREF		●		●	●
Laboratory tests^e^	●			●	
Chest X-ray scan and ECG	●				
Medication		●	●		
Blindness test				●	

*ECG* electrocardiogram, *WHOQOL-BREF* World Health Organization Quality of Life Scale Abbreviated Version

^a^Height and weight, but only weight for visit 2 and follow-up

^b^Age, job, digestion, exercise, smoking habit, drinking habit, sleep pattern, etc.

^c^Including general medical history and history related to cold hypersensitivity in the hands and feet

^d^Temperature measurement of both PC8 and LU4 at every visit and both ST32 and LR3 at visit 2

^e^Screening: hematological examination (white blood cells, red blood cells, hemoglobin, platelet), blood chemistry test (blood urea nitrogen, creatinine, aspartate aminotransferase, alanine aminotransferase, gamma-glutamyl transpeptidase, glucose), thyroid function test (free thyroxine, thyroid-stimulating hormone), urine test, pregnancy test (urine human chorionic gonadotropin). Visit 4: hematological examination (white blood cells, red blood cells, hemoglobin, platelet), blood chemistry test (blood urea nitrogen, creatinine, aspartate aminotransferase, alanine aminotransferase, gamma-glutamyl transpeptidase)

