**Methods:**

This study will be a pilot, randomized, double-blind, two-arm, placebo-controlled, parallel-group, multicenter clinical trial. Women aged 19–59 years who present with CHHF will be recruited from five university hospitals. A total of 60 subjects will be randomly assigned to a treatment group (SDT) or a placebo group at a 1:1 ratio. The subjects will receive 3 g of either SDT or placebo three times daily for 8 weeks. The primary outcome measures will be the Visual Analogue Scale scores of CHHF. The secondary outcome measures will be changes in body temperature in both the hands and the feet as measured using a thermometer and the Korean version of the World Health Organization Quality of Life Scale Abbreviated Version.

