2.2.2. Symptoms of excessive CHHF at a temperature that one can feel cold	
2.2.3. Those who have symptoms of CHHF that do not recover easily when moving from a cold to a warm environment	
3. Those with a Visual Analogue Scale score of ≥ 4 cm at the screening visit	
4. At the screening visit, those who have a thermal difference of ≥ 0.3 °C between the palm (PC8) and the upper arm (LU4) as measured by a thermometer after room temperature adjustment at 24 ± 2 °C for 10 min.	
5. Those who can be observed during the clinical trial	
6. Those who agree to participate and provide written informed consent	

*CHHF* cold hypersensitivity in the hands and feet

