#### Secondary outcome measure

The change in the BT and WHOQOL-BREF score between visit 2 (baseline) and visit 4 (after treatment) will be used as the secondary outcome measure. The mean difference between the change scores of the two groups will be calculated.

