#### BT: thermometer measurement

After 20 min of relaxation at 24 ± 2 °C, the BT will be measured by thermometer (835-T1; Testo, Lenzkirch, Germany) at acupoints PC8 and LU4 at every visit and at ST32 and LR3 at visits 2, 3, 4, and 5.

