### Statistical analysis

#### Efficacy assessment

For the efficacy assessment of this trial, both intention-to-treat (ITT) and per-protocol (PP) analyses will be performed. Missing data will be adjusted using the last-observation-carried-forward (LOCF) imputation method on ITT analysis. For the safety assessment of this trial, PP analysis will be conducted. The continuous variables will be expressed as the mean ± SD and the nominal variables will be reported as percentages. The ITT method will include all randomly assigned subjects, regardless of any protocol violations or study dropouts. The PP method will include only the subjects who have completed the 12-week study period without any major protocol violations and who have a compliance rate of ≥ 70%. The baseline characteristics will be compared by either a chi-square test for nominal variables or analysis of variance (ANOVA) for continuous variables. For the within-group analysis, the primary and secondary outcome variables will be assessed using a paired *t* test. The between-groups analysis after 8 weeks of administration will be performed using a repeated-measure ANOVA for the primary outcome variables, and a paired *t* test for the mean difference in the VAS score between the SDT group and the placebo group. As a secondary outcome variable, the mean differences in BT and WHOQOL-BREF scores between the groups will be analyzed using a repeated-measure ANOVA for BT and an ANOVA and post-hoc analysis for the WHOQOL-BREF scores. For all non-normal distribution data, a nonparametric statistical test will be performed. SPSS for windows version 23.0 (SPSS Inc., Chicago, IL, USA) will be used for statistical analysis. The statistical significance level will be set at *P* < 0.05.

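### Table 4 footnote d schedules ST32 and LR3 at visit 2 only, but the outcome text schedules them at visits 2 to 5; a site that follows the footnote has no change in temperature at those points

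*Protocol article*

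**What the plan says.** **Which sites at which visits.** In Table 4 (Study schedule) the thermometer row is marked at all five visits, and footnote d assigns measurement points to visits: "Temperature measurement of both PC8 and LU4 at every visit and both ST32 and LR3 at visit 2". The section BT: thermometer measurement instead places the readings "at acupoints PC8 and LU4 at every visit and at ST32 and LR3 at visits 2, 3, 4, and 5".

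**What the readings are for.** The section on the secondary outcome defines it as the change, from baseline at visit 2 to the end of treatment at visit 4, in body temperature and in quality of life. The abstract describes the temperature part as "changes in body temperature in both the hands and the feet as measured using a thermometer". The Efficacy assessment section plans a "repeated-measure ANOVA for BT".

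**Acclimatisation.** Inclusion criterion 4 (Table 1) takes the screening difference between PC8 and LU4 "as measured by a thermometer after room temperature adjustment at 24 ± 2 °C for 10 min". The measurement section, which covers PC8 and LU4 at every visit, begins "After 20 min of relaxation at 24 ± 2 °C".

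**The concern.** A change from visit 2 to visit 4 needs a reading at both visits. Footnote d provides one of the two for ST32 and LR3. The schedule table is the usual working reference at a site, and this footnote sets one pair of points at every visit against another pair at a single visit. Read alone, it is a clear instruction and not an evident abbreviation.

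At stake is whether the data for part of a named secondary outcome exist. A skin temperature not taken at visit 4 cannot be reconstructed. Nor would the planned handling of missing data help: last observation carried forward would carry the visit 2 value to visit 4 and impute a change of exactly zero in both arms. Data are collected on paper, with double entry only after the trial is completed, so a gap might not show in the database until it is too late to act. The Trial status section reports 50 participants already recruited.

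The acclimatisation conflict matters less. Two waiting times are stated for the same points at the same visit, and that reading is judged against an eligibility limit of 0.3 °C.

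**Working it through.** The article gives no figure to reproduce here, so the check is a comparison of the passages.

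**Step 1. Are visits 2 and 4 both scheduled?**

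| Point | Table 4, footnote d | BT: thermometer measurement | Change V2 to V4 under footnote | Change V2 to V4 under text |
|---|---|---|---|---|
| PC8 | visits 1–5 | visits 1–5 | yes | yes |
| LU4 | visits 1–5 | visits 1–5 | yes | yes |
| ST32 | visit 2 | visits 2–5 | **no** | yes |
| LR3 | visit 2 | visits 2–5 | **no** | yes |

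The two sources agree on PC8 and LU4 and disagree on ST32 and LR3. The marks in the thermometer row do not settle it, because they apply to the row as a whole and only the footnote separates the points.

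**Step 2. Which schedule fits the rest of the article?** The outcome definition needs visits 2 and 4. The abstract names both hands and feet. A repeated-measures analysis needs more than one time point. All three fit the measurement section; at ST32 and LR3 none fits the footnote.

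**Step 3. Are ST32 and LR3 the foot measurement?** Inclusion criterion 4 identifies PC8 as the palm and LU4 as the upper arm. The article does not say where ST32 and LR3 lie. That they supply the lower-limb part of the outcome is an inference from the abstract's mention of the feet and from the absence of any other points.

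**Step 4. How much could be lost?** This depends on how many of the five sites follow the footnote, which is unknown. As an illustration only, assume equal recruitment, 60 / 5 = 12 participants per site, and ignore dropout. If k sites follow the footnote, 12k participants lack the change at ST32 and LR3, and the standard error of the treatment difference at those points grows by √(60 / (60 − 12k)):

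- k = 0: none missing, factor 1.00
- k = 1: 12 of 60 missing, factor √(60/48) = 1.12
- k = 2: 24 of 60 missing, factor √(60/36) = 1.29
- k = 5: 60 of 60 missing, no estimate

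**Step 5. Acclimatisation.** At visit 1 the PC8 and LU4 reading falls under 10 minutes (criterion 4) and under 20 minutes (measurement section). At visits 2 and 4 only the 20-minute rule applies. The change score uses visits 2 and 4, so the conflict does not enter it.

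**The case against.** The strongest reply is that the intended schedule can be recovered from the article. The section that defines the measurement lists visits 2, 3, 4 and 5, and the outcome definition, the abstract and the planned analysis all agree with it. One footnote stands alone and may be a truncated copy of that text. The article is also a condensed account: the active protocol version and the case report forms are not shown, and nothing in it indicates that any site omitted a reading. This stands, and it limits the point to a contradiction with a conditional consequence.

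A reader might infer that the change in foot temperature cannot be computed at all, or that all 60 participants lack it. The documents do not support that; it would require every site to follow the footnote against the measurement section. Nor do they support saying that half of the outcome is lost, because ST32 and LR3 are never located and one of them could be a proximal reference point.

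A reader might also fear bias if sites differ in practice. Randomization is 1:1 and stratified by hospital in blocks of two and four, so missingness by site would fall about equally on the two arms. The expected cost is precision; no bias in the treatment comparison is shown.

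On acclimatisation, the article gives no figure for how the difference between PC8 and LU4 moves between 10 and 20 minutes, so an effect on eligibility cannot be sized. Setting 10 minutes beside 0.3 °C does not size it.

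What survives is that both instructions are in the current text, they cannot both be followed, and readings missed under one of them are gone.

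**Conclusion.** The contradiction is real, and it is more than clerical because it decides whether part of a secondary outcome is collected. Where a site follows footnote d, the change from visit 2 to visit 4 at ST32 and LR3 is unavailable and cannot be recovered; where it follows the measurement section, nothing is lost. Across sites the loss can lie anywhere from none to all participants for these two points, and only the completed case report forms can show which. The relevance to the feet rests on the inference in step 3.

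The primary VAS outcome, the sample size and the readings at PC8 and LU4 are untouched. The 10 against 20 minute conflict is a minor point confined to the screening reading. Rating: should be fixed, as an internal inconsistency affecting a secondary outcome in a pilot trial.

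**What to change.** 1. Correct Table 4 footnote d to match the measurement section: PC8 and LU4 at every visit; ST32 and LR3 at visits 2, 3, 4 and 5.
2. Notify the five sites of the correction.
3. Check the case report forms completed so far for the schedule each site used, and report the number of participants with ST32 and LR3 readings at both visit 2 and visit 4, by site and arm.
4. Reconcile inclusion criterion 4 with the measurement section on acclimatisation, and record the time actually used at screening.

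Items 1 to 3 cost one footnote, a memo, a review of forms already held and, at any site that had followed the footnote, a few minutes per visit with a thermometer already in use. Item 4 needs more care. With 50 of 60 participants recruited, changing the screening procedure could put the remaining 10 under a different entry condition and would alter an eligibility criterion in mid-trial. Stating which time has applied may be enough.
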